#### *Study summary*

The study will allow for collection of important data on the feasibility of an intermittent/daily PrEP regimen in HIV discordant couples, and it will directly compare adherence and intracellular drug levels in daily and intermittent PrEP recipients. It will also evaluate the relationship between drug adherence, sexual behaviour and intracellular drug levels with an intermittent PrEP regimen. Specifically, this study will use timed plasma and intracellular drug levels after a witnessed dose and MEMS adherence data to model drug levels. This model can explore relationships between adherence and intracellular drug levels to determine if intracellular drug levels can be used as a surrogate adherence measure. In addition it will evaluate the relationship between adherence to an intermittent PrEP regimen and timing of sexual activity to estimate what proportion of sexual events may be 'protected' by intermittent PrEP. The pilot will use objective MEMS adherence measurement and evaluate the feasibility of newer adherence measurements such as hair sampling and plasma drug levels. The pilot will also evaluate the feasibility of using either IVR or SMS to collect sexual activity data in an African setting. It will allow study teams and communities to prepare for potential subsequent larger trials of intermittent PrEP. The pilot study is not sized to evaluate efficacy. If the pilot shows this intermittent PrEP regimen to be safe, feasible in terms of adherence, and to achieve intracellular drug levels similar to daily PrEP, this data could be used to design a larger phase 2 study with one or more intermittent PrEP regimens. The goal of such a trial would be to provide bridging data if daily PrEP regimens are found to be effective or to prepare for efficacy or non-inferiority trials of intermittent versus daily PrEP.

Investigation of immune responses associated with FTC/TDF will also be evaluated in the pilot study. The proportion of volunteers on FTC/TDF with HIV-specific immune responses will be assessed at 2-3 time points and compared to responses in volunteers assigned to placebo. Immune responses may be correlated with risk behaviour and host factors, such as HLA type. As noted above, very few HIV infections are expected to occur during the study, so correlation of HIV-specific immune responses and protection from infection or attenuation of disease progression will not be possible until a larger study is conducted.

## **4.0 STUDY OBJECTIVES**

### **4.1 Primary Objectives**

To evaluate the safety of daily and intermittent dosing (twice a week and within 2 hours after sex with no more than one dose per day) of FTC/TDF

To compare the acceptability of and adherence to daily and intermittent regimens

To evaluate mean intracellular drug concentrations in the daily and intermittent regimens

To evaluate the relationship between adherence and intracellular drug levels

To evaluate changes in HIV-associated risk behaviour

### **4.2 Other Objectives**

To prepare study teams for larger PrEP trials

To evaluate methods for measuring adherence and sexual activity

To evaluate potential for medication sharing

To evaluate HIV-specific immune responses in volunteers randomized to FTC/TDF and to placebo

## **5.0 STUDY ENDPOINTS AND STUDY DESIGN**

### **5.1 Study Endpoints**

#### **5.1.1 Primary Endpoints**

##### *Safety and tolerability:*

- The proportion of volunteers with moderate and greater severity clinical adverse events
- The proportion of volunteers with mild, moderate and greater severity of renal toxicities, and other moderate and severe laboratory abnormalities
- The proportion of volunteers with serious adverse events

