#### **5.2.3 Inclusion Criteria for HIV-uninfected volunteers**

1. Healthy male or female, as assessed by a medical history and physical exam
2. At least 18 years of age on the day of screening and not older than 49 years on the day of randomization;

3. Willing to comply with the requirements of the protocol and available for follow-up for the planned duration of the study;
4. In the opinion of the Principal Investigator or designee, has understood the information provided and has provided written informed consent before any study-related procedures are performed;
5. Willing to undergo couple HIV testing, STI screening, HIV counseling and receive test results, and share results with partner
6. At risk for HIV infection as defined by at least one of the following: HIV-infected partner not using ART in the past 3 months and had episodes of unprotected vaginal sex with partner in the past 3 months
7. If a female of childbearing potential (i.e., not post-menopausal or surgically sterile), using an effective method of non-barrier contraception (hormonal contraceptive; intrauterine device (IUD); surgical sterility) from 7 days prior to randomization until the end of the study. All female volunteers must be willing to undergo urine pregnancy tests at time points as indicated in the Schedule of Procedures (Appendix A1).
8. HIV-infected partner is willing and eligible (see 5.2.5. and 5.2.6.) to enrol in the study

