#### 5.2.4 Exclusion Criteria for HIV-uninfected volunteer

1. Confirmed HIV-1 or HIV-2 infection
2. Any clinically significant acute or chronic medical condition that is considered progressive or in the opinion of the investigator would make the volunteer unsuitable for the study, including severe infections requiring treatment such as tuberculosis, and alcohol or drug abuse.
3. Any of the following abnormal laboratory parameters:
  - Haemoglobin <9.0 g/dL
  - Creatinine clearance <60mL/min, as calculated by Cockcroft-Gault equation:

CrCl in mL/min =

Males:  $\frac{(140 - \text{age in years}) \times (\text{wt in kg})}{72 \times (\text{serum creatinine in mg/dL})}$

Females:  $\frac{(140 - \text{age in years}) \times (\text{wt in kg}) \times 0.85}{72 \times (\text{serum creatinine in mg/dL})}$

  - AST: >2.5 x ULN
  - ALT: >2.5 x ULN

- Total bilirubin >1.5 x ULN
  - Serum amylase >1.5 x ULN
  - Serum phosphorus <2.4 mg/dL
  - Urinalysis: Two abnormal dipsticks showing any of the following:
    - blood = 2+ or more (not due to menses);
    - protein = 1+ or more
    - leucocytes = 2+ or more
    - glucose= 1+ or more
4. Confirmed diagnosis of chronic hepatitis B infection (HbsAg positive)
  5. If female, pregnant or planning a pregnancy within 4 months after enrolment or lactating.
  6. Participation in another clinical study of an investigational product currently, within the 3 months prior to enrolment or expected participation during this study

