**9.0****ASSESSMENTS****9.1 Safety and Tolerability Assessments****9.1.1 Clinical adverse events**

Occurrence of clinical adverse events (including Serious Adverse Events) will be collected following an open question to volunteers on the time points according to the Schedule of Procedures (Appendix A1). The adverse events will be graded using the Appendix B, Adverse Event Grading Toxicity Table as a guideline. For more information regarding adverse events refer to Section 10.0, Adverse Events.

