## 12.0 **DISCONTINUATION OF ADMINISTRATION OF INVESTIGATIONAL PRODUCT AND/OR WITHDRAWAL FROM STUDY**

### 12.1 **Discontinuation of administration of investigational product**

Any volunteer discontinuing from investigational product or being considered for discontinuation of investigational product will be discussed with the sponsor. Volunteers will be discontinued from investigational product for any of the following reasons:

1. Pregnancy
2. Intercurrent HIV infection
3. A disease or condition or an adverse event that may develop, regardless of relationship to the investigational product, if the principal investigator or designee is of the opinion that further investigational product is not in the best interest of the volunteer.
4. Use of antiretroviral medications or other medications that may interact with investigational product
5. Volunteer request to discontinue further participation.
6. Participating in another clinical study of an investigational product
7. Creatinine clearance (CrCl)  $\leq 50$  mL/min, as calculated by Cockcroft-Gault formula
8. Any of the other following abnormal laboratory parameters that occur after randomization:

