**Serum Creatinine Elevation**

All Grades

Continue study medication for up to 3 days while values are confirmed

Confirmed Grade 1

Continue study medication at the discretion of the study physician  
Monitor weekly until return to within 0.3 mg/dL of the baseline value

Confirmed Grade 2-4

Permanently discontinue study drug  
Monitor as clinically indicated (generally at least monthly up to 3 months) until return to within 0.3 mg/dL of the baseline value

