**Quick Reference**

The Division of AIDS Table for Grading the Severity of Adult and Pediatric Adverse Events ("DAIDS AE grading table") is a descriptive terminology which can be utilized for Adverse Event (AE) reporting. A grading (severity) scale is provided for each AE term.

**General Instructions**Estimating Severity Grade

If the need arises to grade a clinical AE that is not identified in the DAIDS AE grading table, use the category "Estimating Severity Grade" located at the top of Page 3. For AEs that are not listed in the table but will be collected systematically for a study/trial, protocol teams are highly encouraged to define study specific severity scales within the protocol or an appendix to the protocol. (Please see "Template Wording for the Expedited Adverse Event Reporting Section of DAIDS-sponsored Protocols".) This is particularly important for laboratory values because the "Estimating Severity Grade" category only applies to clinical symptoms.

Grading Adult and Pediatric AEs

The DAIDS AE grading table includes parameters for grading both Adult and Pediatric AEs. When a single set of parameters is not appropriate for grading specific types of AEs for both Adult and Pediatric populations, separate sets of parameters for Adult and/or Pediatric populations (with specified respective age ranges) are given in the table. If there is no distinction in the table between Adult and Pediatric values for a type of AE, then the single set of parameters listed is to be used for grading the severity of both Adult and Pediatric events of that type.

Determining Severity Grade

If the severity of an AE could fall under either one of two grades (e.g., the severity of an AE could be either Grade 2 or Grade 3), select the higher of the two grades for the AE.

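### The primary renal endpoint does not say which measures count, and its grading table has no creatinine-clearance grade although clearance is a stopping criterion

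*Protocol*

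**What the plan says.** The renal part of the primary safety endpoint (Protocol 5.1.1, repeated in the synopsis) is "The proportion of volunteers with mild, moderate and greater severity of renal toxicities, and other moderate and severe laboratory abnormalities". Renal events count from mild upward and other laboratory abnormalities only from moderate. No renal parameter is named.

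On grading, section 9.1.1 states: "The adverse events will be graded using the Appendix B, Adverse Event Grading Toxicity Table as a guideline". Section 10.2 also refers laboratory abnormalities to that table. Appendix B starts creatinine Grade 1 at 1.1 x ULN, with a footnote asking for age- and sex-appropriate values. It also grades low serum phosphate, proteinuria and haematuria. It has no row for creatinine clearance and none for a creatinine rise from the volunteer's own baseline. Its general instructions encourage study-specific scales for events collected systematically but not listed. They add "This is particularly important for laboratory values because the" row for estimating severity is a "category only applies to clinical symptoms". The protocol supplies no such scale for clearance.

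Clearance is nonetheless used throughout:
- Entry (5.2.4) excludes "Creatinine clearance <60mL/min, as calculated by Cockcroft-Gault equation".
- Section 3.5 names estimated clearance as the means of renal monitoring.
- Table 3 and Appendix A1 place it in the chemistry panel at screening and Weeks 4, 8 and 16.
- Section 12.1 item 7 makes a value at or below 50 "mL/min, as calculated by Cockcroft-Gault formula" a reason to discontinue product.

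The separate creatinine rule in 12.1 says of a confirmed Grade 1: "Continue study medication at the discretion of the study physician".

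**The concern.** The endpoint is a count of graded events, but the measure used for entry, monitoring and stopping carries no grade. Clearance depends on age, weight and sex as well as creatinine, whereas the Appendix B creatinine grade depends only on the ratio to ULN. In a light volunteer, clearance can reach the stopping value while creatinine is still below the lowest grade. Such a volunteer could leave product for a renal reason and be scored as having no renal toxicity.

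Section 3.3.1 discusses renal toxicity of TDF at length and lists low body weight among its risk factors, and the endpoint is set to catch even mild renal events. The volunteers whom the table serves least well therefore include a group that the protocol itself regards as at higher risk.

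**Working it through.** **The plan's own precision figure.** Section 14.2.1 gives exact 95% intervals for an arm of 24. For 0/24 the upper limit is 1 - 0.025^(1/24) = 0.1425. For 1/24 the Clopper-Pearson interval is (0.0011, 0.2112). Both are reproduced. No stated figure rests on the renal grading itself.

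**Inputs.**
- Clearance formula and entry limit of 60 mL/min: 5.2.4
- Age from 18, and "not older than 49 years on the day of randomization": 5.2.3
- Stopping value of 50 mL/min: 12.1 item 7
- Lowest creatinine grade, 1.1 x ULN: Appendix B
- ULN in mg/dL: not given. The table below assumes 1.0 to 1.2, and 0.9 to 1.4 was also checked.

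**Formula.** CrCl = (140 - age) x weight x k / (72 x creatinine), with k = 0.85 for women and 1 for men. Creatinine at CrCl 50 is (140 - age) x weight x k / 3600. The result is ungraded when this is below 1.1 x ULN.

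**Main example.** Woman, 40 years, 45 kg: 100 x 45 x 0.85 = 3825.
- Entry at 0.70 mg/dL: 3825 / (72 x 0.70) = 75.9 mL/min, eligible.
- Later at 1.07 mg/dL: 3825 / (72 x 1.07) = 49.6 mL/min, so item 7 is met.
- Creatinine ratio: 1.07, 0.97 and 0.89 x ULN at ULN 1.0, 1.1 and 1.2. All are below 1.1, so there is no creatinine grade. At ULN 0.9 the ratio is 1.19, which is Grade 1.

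**Other volunteers, at CrCl exactly 50.**

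| Volunteer | Creatinine (mg/dL) | x ULN at 1.0 / 1.1 / 1.2 | Creatinine grade |
|---|---|---|---|
| Woman, 49 y, 45 kg | 0.97 | 0.97 / 0.88 / 0.81 | none (1.07 x at ULN 0.9, also none) |
| Woman, 40 y, 50 kg | 1.18 | 1.18 / 1.07 / 0.98 | Grade 1 / none / none |
| Man, 49 y, 50 kg | 1.26 | 1.26 / 1.15 / 1.05 | Grade 1 / Grade 1 / none |
| Man, 30 y, 60 kg | 1.83 | 1.83 / 1.67 / 1.53 | graded throughout (1.31 x even at ULN 1.4) |

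**Weight limits for women.** The limit is 50 x 72 x 1.1 x ULN / ((140 - age) x 0.85). Below it, CrCl can reach 50 ungraded. At ULN 1.0, 1.1 and 1.2 it is about 44, 49 and 53 kg at age 35, and 49, 54 and 59 kg at age 45.

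**Loss of half of clearance.** At fixed age and weight, halving clearance doubles creatinine. The change is ungraded when 2 x baseline < 1.1 x ULN, that is, baseline < 0.55 x ULN: 0.55 mg/dL at ULN 1.0 and 0.66 at ULN 1.2. Example: woman, 30 y, 60 kg, creatinine from 0.6 to 1.2 mg/dL, clearance from 130 to 65 mL/min. The ratio is 1.09 x at ULN 1.1 and 1.00 x at ULN 1.2 (ungraded), but 1.20 x at ULN 1.0 (Grade 1).

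**Effect on the count.** One missed case in 24 is 1/24 = 4.2 percentage points. It turns 1/24 (upper limit 21.12%) into 0/24 (14.25%).

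**The case against.** Several defences of the plan are sound and limit the point.

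A reader might infer that renal toxicity is graded on serum creatinine alone. The documents do not say so. Low phosphate is graded in Appendix B and measured on treatment, and section 3.3.1 lists it among the features of TDF renal dysfunction. The urine rows add little in practice, because dipstick testing is scheduled at screening only. Phosphate does not substitute for clearance, so the gap remains.

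A reader might also infer that a clearance fall has no route to a grade. Appendix B is used as a guideline, section 10.1 allows an abnormal laboratory finding to be an adverse event, and section 10.2 leaves severity finally to the principal investigator. A fall could be reported and graded. What stands is that no criterion is given, so one investigator may grade it and another may not.

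A further tempting reading is that the two stopping rules in 12.1 contradict each other. They are alternative triggers. Item 7 suffices alone, and discretion at Grade 1 does not forbid stopping. Likewise, the 0.3 mg/dL margin says how long to monitor creatinine. It does not define an event, and nothing supports using it as an endpoint threshold.

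Finally, a stop should appear in the tabulation of discontinuation reasons (14.2.1), and all routine laboratory data enter the safety analysis. Listing parameters can often be left to an SAP, which is not at hand. But here the protocol itself fixes the endpoint, the grading table and a renal stopping criterion outside that table.

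**Conclusion.** The point holds in limited form. The primary renal endpoint does not define renal toxicity, and its grading table has no clearance grade and no baseline-relative creatinine grade, although clearance governs entry, monitoring and one stopping reason. Followed as written, some low-weight or older volunteers can meet the clearance stopping criterion without an Appendix B creatinine grade. Some with low baseline creatinine can lose about half of clearance ungraded.

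How often this would happen cannot be stated. It depends on a ULN that the protocol does not give and on weights and baseline creatinine values that are unknown. Heavier and younger volunteers are graded well before clearance reaches 50. One case matters in an arm of 24: an upper limit of 14.25% instead of 21.12%.

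A reader might go on to conclude that the misses fall mainly in the FTC/TDF arms and bias the safety result toward no effect. No figure in the protocol supports that direction. A volunteer entering near 60 mL/min could cross 50 in any arm.

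**What to change.** In 5.1.1, the synopsis and 14.2.1, state that renal toxicity means either an Appendix B Grade 1 or higher creatinine or low-phosphate result, or any confirmed creatinine clearance that meets the protocol's own criterion in 12.1 item 7. Report change in clearance from baseline by arm, so that large ungraded falls are visible.

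Separately, for clarity, item 7 and the creatinine rule in 12.1 should be reconciled on how both apply to the same result, including confirmation, which the creatinine rule mentions and item 7 does not. No view is taken here on which stopping rule is right.

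The cost is endpoint wording and one derived variable. Creatinine, clearance and phosphate are already scheduled at screening and Weeks 4, 8 and 16. The downside is a slightly higher reported renal event rate.

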### **10.2 Assessment of Severity of Adverse Events**

Assessment of severity of all AEs is ultimately the responsibility of the principal investigator.

The following general criteria should be used in assessing adverse events as mild, moderate, severe or potentially life-threatening:

- Mild: Mild discomfort; Minimal or no limitation of daily activities; Medical intervention not required;

- Moderate: Moderate discomfort; Some limitation of daily activities but able to work part-time or full-time with some assistance; May require minimal or no medical intervention;
- Severe: Severe discomfort; Marked limitation of daily activities, unable to work; Requires medical intervention;
- Very severe (listed as “potentially life threatening” in Appendix B): Extreme limitation in activity, significant assistance required, significant medical intervention therapy required, hospitalization required

Guidelines for assessing the severity of specific adverse events and laboratory abnormalities are listed in Appendix B, Adverse Event Severity Assessment Table.

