#### **17.1.1 Content of Interim Review**

The SRB will be asked to review the following data:

- A blinded listing of all severe clinical adverse events, independent of relationship to the Investigational Product, and
- A blinded listing of all severe laboratory adverse events confirmed on retest, independent of relationship to the Investigational Product, and
- A blinded listing of all Serious Adverse Events, independent of relationship to the Investigational Product.

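### The non-renal part of the primary laboratory safety endpoint stops at Grade 3 as worded, and a Grade 4 laboratory value that is not an SAE is in none of the Safety Review Board's lists

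*Protocol*

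**What the plan says.** Section 5.1.1 of the protocol, repeated in the synopsis, sets three safety endpoints. The clinical one is "The proportion of volunteers with moderate and greater severity clinical adverse events". The laboratory one begins "The proportion of volunteers with mild, moderate and greater severity of renal toxicities" and continues, in the same bullet, "and other moderate and severe laboratory abnormalities". The third is the proportion with serious adverse events.

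Section 10.2 sets the severity scale: its general criteria "should be used in assessing adverse events as mild, moderate, severe or potentially life-threatening". The fourth level is defined separately from the third, as "Very severe (listed as “potentially life threatening” in Appendix B". Appendix B gives each grade its own column, with severe as Grade 3 and potentially life-threatening as Grade 4.

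Section 17.1.1 sends the Safety Review Board three listings: severe clinical events, serious adverse events of any grade, and "A blinded listing of all severe laboratory adverse events confirmed on retest".

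**The concern.** One bullet changes its wording midway. Clinical events and renal toxicities are counted from a stated grade upward. Other laboratory abnormalities are counted at two named levels of a four-level scale. Followed to the letter, a Grade 2 liver enzyme or neutrophil value counts toward a primary safety endpoint and a Grade 4 value of the same test does not.

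The SAE endpoint need not pick up such a value, because the seriousness criteria in Section 10.4 are clinical outcomes and name no laboratory grade. The Board's laboratory listing has the same closed wording. Two things are at stake: whether a primary endpoint is computed as intended, and whether the Board is sure to be shown the most extreme laboratory values.

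**Working it through.** The plan gives no figure for this endpoint, so the check is mainly a comparison of texts.

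**1. Which grades each phrase covers**

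| Place | Item | Grades as worded |
|---|---|---|
| 5.1.1 and synopsis | Clinical adverse events | 2, 3, 4 |
| 5.1.1 and synopsis | Renal toxicities | 1, 2, 3, 4 |
| 5.1.1 and synopsis | Other laboratory abnormalities | 2, 3 |
| 17.1.1 | Clinical listing | 3 |
| 17.1.1 | Laboratory listing | 3 |
| 17.1.1 | SAE listing | any grade, if an SAE |

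**2. Is severe a single grade in this protocol?** Section 10.2 and Appendix B treat it as one. The Appendix B laboratory cut-offs are separate: ALT 5.1–10.0 x ULN is Grade 3 and above 10.0 x ULN is Grade 4; neutrophils 500–749/mm³ are Grade 3 and below 500/mm³ are Grade 4. Where Section 12.1 means both upper grades it gives both numbers, and it treats a confirmed Grade 3 and a confirmed Grade 4 differently.

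**3. Does another route catch a non-renal Grade 4 laboratory value?**
- *SAE endpoint and SAE listing:* only if an SAE criterion in Section 10.4 is met.
- *Final safety tables:* yes. Section 10.1 counts an abnormal laboratory finding as a possible adverse event. Section 14.2.1 tabulates adverse events by treatment group and grade, and takes all routine laboratory data into the safety analysis.
- *The endpoint numerator and the Board's laboratory listing:* no. The tabulation redefines neither.

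**4. Does another route catch a Grade 4 clinical event for the Board?** Mostly yes. The Section 10.2 description of the fourth level includes "significant medical intervention therapy required, hospitalization required", and in-patient hospitalization is an SAE criterion in Section 10.4. Such events reach the Board through the SAE listing. A few Appendix B entries, such as fatigue and insomnia, reach Grade 4 on inability to perform basic self-care alone, so the route is not complete.

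**5. Who is missed by the endpoint?** The endpoint is per volunteer. A volunteer is missed only with all of the following:
- at least one non-renal Grade 4 laboratory value;
- no non-renal Grade 2 or 3 laboratory value recorded at any time;
- no renal toxicity of any grade recorded at any time.

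For volunteers who stay HIV-uninfected, Appendix A1 schedules post-randomization haematology and chemistry at Weeks 4, 8 and 16, so a Grade 4 value can appear without an earlier lower-grade one. Section 12.1 requires follow-up of confirmed Grade 4 toxicity until it resolves, up to study closure, so a later Grade 2 or 3 value may bring the volunteer into the count.

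**6. Scale, for illustration.** Inputs: n = 24 per FTC/TDF arm (Section 14.2.1) and an assumed single volunteer of the kind in step 5. Exact Clopper-Pearson 95% limits:
- 0/24: lower 0; upper 1 − 0.025^(1/24) = 0.1425.
- 1/24 = 0.0417: lower 1 − 0.975^(1/24) = 0.0011; upper = the 97.5th percentile of Beta(2, 23) = 0.2112.

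These are the intervals Section 14.2.1 prints for zero and one drug-related SAE, so the method reproduces the protocol's own figures. Under the literal wording the arm reports 0/24 (0 to 14.25%). Under open-ended wording it reports 1/24 = 4.2% (0.11% to 21.12%).

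**The case against.** The best counter-argument is that nobody would apply the wording literally. The protocol also calls the top level very severe, and in ordinary English a very severe event is a severe one. A list of all severe events that left out the worst is not what the authors meant, and table cut-offs are often settled in the analysis plan, which is not shown. That is fair as a guess at intent. It does not remove the mismatch: the same bullet uses open-ended wording for renal toxicities, and the document uses severe as the name of one grade. A primary endpoint should not depend on the reader correcting it.

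A reader might infer three stronger things, and the documents do not support them.
- *Grade 4 drops out of the laboratory endpoint altogether.* Renal toxicities are counted at every grade, and renal toxicity is the risk that Sections 3.3.1 and 3.5 discuss and plan to monitor closely.
- *Grade 4 laboratory values go unreported.* Section 14.2.1 tabulates by grade and reports discontinuations with reasons by group, so these values should be visible by arm in the final report.
- *The Board has the same gap for clinical events.* The SAE listing carries most of them. The suspension trigger in Section 17.1.2 is based on related SAEs and does not depend on this wording.

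It is also right that the 1/24 against 0/24 contrast is a constructed case. The protocol gives no rate of Grade 4 laboratory values, and step 5 shows how specific the missed volunteer must be.

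**Conclusion.** The point holds in a limited form. As worded, the non-renal part of the primary laboratory endpoint covers Grades 2 and 3 only, which conflicts with the clinical and renal parts beside it and with the four-grade scale. In Section 17.1.1, a confirmed Grade 4 laboratory value that meets no SAE criterion belongs to none of the three listings.

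This is an error of wording with low impact. It touches only volunteers whose sole qualifying abnormality is a non-renal Grade 4 value, and for the Board only Grade 4 laboratory values that are not SAEs, with a small remainder of clinical events. The conclusion assumes that severe carries its Section 10.2 and Appendix B meaning wherever it is used as a category. No sample size, power or interval stated in the protocol changes.

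**What to change.** - **Section 5.1.1 and the synopsis:** replace the closing phrase of the laboratory endpoint with *other laboratory abnormalities of moderate or greater severity (Grade 2–4)*.
- **Section 17.1.1:** in the laboratory listing, replace severe with *severe or greater (Grade 3 or 4)*. Make the same change in the clinical listing for consistency.

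The cost is a few words. No assessment, visit or sample is added. The endpoint proportion can only stay the same or rise, and the Board's listings can only stay the same or lengthen.
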